### 2.8. Intervention Conditions

#### 2.8.1. Experimental Condition

At colleges/universities assigned to the experimental condition, participating pre-service ECEs will be required to complete the 4-module e-Learning course (in-class or at home, up to the instructor’s discretion) within a 4-week timeframe.

#### 2.8.2. Comparison Condition

Colleges/universities assigned to the comparison group will continue their typical curriculum for the duration of the study. Upon completion of the study, students in the comparison group may opt to offer the e-Learning course to their pre-service ECEs. Pre-service ECEs in the comparison group will complete the same study instruments as those in the experimental group (with the exception of the process evaluation survey and interviews).

### 2.9. Primary Outcome Measures

Various tools will be used to assess the impact of the TEACH study on pre-service ECEs’ physical-activity and sedentary behaviour-related self-efficacy and knowledge. See Table 1 for a description of tools and administration.

#### 2.9.1. Pre-Service ECEs’ Physical Activity and Sedentary Behaviour-Related Self-Efficacy

Our research team systematically reviewed physical activity and sedentary behaviour-related self-efficacy tools for ECEs; based on the findings from this review, no such tool emerged from the literature to meet the specific needs of this project [40]. Consequently, we created a 31-item questionnaire to assess ECEs’ Confidence in Outdoor Movement, Physical Activity, and Sedentary and Screen behaviours (*ECE-COMPASS*) [40]. This questionnaire, created by our team using Bandura’s Guide for Constructing Self-Efficacy Scales [41], assesses task (21 items) and barrier (10 items) self-efficacy and showed high internal consistency (Cronbach’s alpha > 0.90 across task and barrier subscales) and modest temporal stability (test-retest statistics > 0.60) [40]. This survey will be administered online at baseline, post-intervention, and 3-month follow-up, and composite scores for task and barrier self-efficacy will be calculated.

#### 2.9.2. Pre-Service ECEs’ Physical Activity and Sedentary Behaviour-Related Knowledge

As no validated tool exists to examine pre-service ECEs’ physical activity or sedentary behaviour-specific knowledge, our team developed a tool to assess this outcome in our study participants by creating questions based upon e-Learning course content (Appendix A). This 22-item online survey will be administered at baseline, post-intervention, and 3-month follow-up, and a composite score will be generated. Psychometric properties will be analysed and reported.

### 2.10. Secondary Outcome Measures

#### 2.10.1. Demographic Characteristics

Participant demographics, including age, gender, ethnicity, college/university, year of study, and program type and delivery method, will be captured via an online survey at baseline. Participants’ self-reported physical activity and recreational screen-viewing levels, previous professional learning courses/webinars in physical activity or sedentary behaviour (i.e., number taken), interest in physical activity and sedentary behaviour education (5-point scale; 0 = not interested at all to 4 = very interested), and previous experience with e-Learning (yes or no) will also be captured at both baseline and post-intervention.

#### 2.10.2. Learning Management System Metrics

E-Learning course completion rates (percent), usage data (completion time per module), and pre-service ECE attrition will be explored within the secure module platform to examine program fidelity. Student answers for module knowledge assessments (i.e., the 12-question assessments completed before proceeding to the subsequent module) will also be examined to measure short-term retention of material. Colleges/universities will be asked to share whether they required students to complete the modules as a course deliverable (produce a certificate of completion). 

#### 2.10.3. Behavioural Intention and Perceived Behavioural Control Survey

The ECEs’ Movement Behavioural Intention and Perceived Control (ECE-MBIPC) questionnaire will be completed by pre-service ECEs at baseline, post-intervention, and 3-month follow-up to gather their perspectives regarding their attitudes toward promoting physical activity and minimizing sedentary behaviour in childcare. This 56-item tool, adapted from Gagné and Harnois [42], is based on the Theory of Planned Behaviour [43] and measures psychosocial variables, including behavioural intention (28 items) and perceived behavioural control (28 items) to promote physical activity and outdoor/risky play, minimize prolonged sedentary time, and avoid screen time in childcare. Seven behaviours are measured for each psychosocial variable, and each behaviour is measured using four items; composite scores will be calculated for each of the seven behaviours for both behavioural intention and perceived behavioural control. Reliability analyses for the ECE-MBIPC tool have demonstrated high internal consistency (Cronbach’s alpha > 0.85) and acceptable temporal stability (>0.70) [44].

#### 2.10.4. Process Evaluation Survey—Pre-Service ECEs

An online process evaluation survey (38 items) will be completed by participants in the experimental group to gather their perspectives on the acceptability (i.e., satisfaction with the course), compatibility (i.e., appropriateness of the course for integration in ECE curricula), usability of the e-Learning platform, complexity of the content, and perspectives regarding suggestions for improvement. The survey will be informed by the Evaluating e-Learning System Success (EESS) model [45] to capture e-Learning-specific perspectives, and additional questions will capture their perspectives on course content.

#### 2.10.5. Process Evaluation Survey—ECE Instructors

An online survey (23 items) will be completed by ECE instructors at each institution in the experimental group to gather their current teaching of physical activity and sedentary behaviour content (including which specific concepts are covered), their perspectives on the course design, content, and implementation, and the feasibility of integrating the e-Learning course into their curricula.

#### 2.10.6. Interviews

A sample of pre-service ECEs (*n* = ~24) and instructors (*n* = ~12) will be interviewed to gain in-depth feedback on the e-Learning course’s implementation, content, and delivery. All interviews will last 30–45 min and will be digitally recorded and transcribed verbatim. A semi-structured interview guide, with probes, will be used to direct the conversation (Appendix B). Interviews will gather pre- and in-service ECEs’ experiences with the e-Learning course (e.g., its functionality, challenges experienced completing the course, and characteristics of the course that best facilitated learning), as well as their perspectives about learning physical activity and sedentary behaviour-related content. Interviews with instructors will gather their perspectives on the e-Learning course content, its alignment with their current early childhood education curriculum, student engagement with the course, and any alterations that would improve the course.

#### 2.10.7. CFIR Checklist

To ensure our intervention is designed and implemented with specific consideration to each of the five domains within the CFIR (e.g., it is evidence-based, stakeholder-supported, and trialled prior to widespread implementation), a checklist, created from the 39 constructs of the CFIR, will be completed by research staff (Appendix C). The research team will document how each construct of the CFIR (e.g., intervention complexity and adaptability, implementation climate, fidelity) is satisfied throughout the intervention (i.e., using data from the needs assessment, the Delphi content development study, website metrics, process evaluation survey, and interviews). Completion of this checklist will be indicative of the scalability of the TEACH study to a wider population.

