### 1.2. Study Objective

The primary objectives of the Training pre-service EArly CHildhood educators in physical activity (TEACH) study are to examine if the e-Learning course increases pre-service ECEs’: 1. self-efficacy to engage children in physical activity and outdoor play, and minimize sedentary behaviour in childcare; and, 2. physical activity and sedentary behaviour-related knowledge. The secondary objectives of the study are to explore: 1. pre-service ECEs’ behavioural intention and perceived behavioural control to promote physical activity and outdoor play and minimize sedentary behaviour in childcare; and, 2. implementation (e.g., fidelity, feasibility, acceptability, pre-service ECEs’ and early childhood education program instructors’ experiences) and potential scalability (via the Consolidated Framework for Implementation Research (CFIR) checklist) of the e-Learning course. 

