A. Structural Characteristics	The social architecture, age, maturity, and size of an organization.	Recruitment of College/University ECE Programs	Yes	The relatively new regulation of the early childhood educator profession has prompted the introduction of more college and university ECE programs. As such, ECE curricula are changing, and reviewed regularly to accommodate new research and foci. The nesting of ECE programs in larger, well-established academic institutions ensures resources are available for these changes.
B. Networks & Communications	The nature and quality of webs of social networks and the nature and quality of formal and informal communications within an organization.	ECE Program Faculty and Staff	Yes	ECE program staff and faculty have strong relationships and work collaboratively to provide ECE students with high-quality educational experiences.
C. Culture	Norms, values, and basic assumptions of a given organization.	College and University Reputation	Yes	Colleges and universities are esteemed to provide high-quality educational experiences and are increasingly using online platforms to deliver course content.
D. Implementation Climate	The absorptive capacity for change, shared receptivity of involved individuals to an intervention, and the extent to which use of that intervention will be rewarded, supported, and expected within their organization.			
1. Tension for Change	The degree to which stakeholders perceive the current situation as intolerable or needing change.	Needs Assessment (Bruijns et al., 2019)	Yes	ECE students communicated that they wished to receive more training in physical activity and sedentary behaviour.
2. Compatibility	The degree of tangible fit between meaning and values attached to the intervention by involved individuals, how those align with individuals’ own norms, values, and perceived risks and needs, and how the intervention fits with existing workflows and systems.	Needs Assessment (Bruijns et al., 2019) Delphi Study (Bruijns et al., 2020)	Yes	The e-Learning course we are developing addresses the gaps in content revealed in the needs assessment by ECE students. The Delphi study with ECE experts highlighted that the content developed for the course aligns with ECE curriculum objectives.

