2. Available Resources	The level of resources dedicated for implementation and on-going operations, including money, training, education, physical space, and time.	e-Learning Course Development (Summer 2020), ECE Instructor Support	--	The e-Learning course will be designed to take ~4 h to complete – a reasonable time requirement to integrate into pre-existing ECE courses. The course will be able to be accessed via mobile phone, tablet, laptop, or desktop, offering flexibility for ECE students. The course will initially be free of cost, and course instructors will be given a brief tutorial on how to use the e-Learning course so they can help their students.
3. Access to Knowledge & Information	Ease of access to digestible information and knowledge about the intervention and how to incorporate it into work tasks.	Communication with ECE Program Staff and Instructors	--	The research team will be readily available to answer any questions from participating ECE programs regarding program implementation.
IV. CHARACTERISTICS OF INDIVIDUALS				
A. Knowledge & Beliefs about the Intervention	Individuals’ attitudes toward and value placed on the intervention as well as familiarity with facts, truths, and principles related to the intervention.	Demographics Survey (Winter 2022)	--	ECE students’ perceived value placed on this type of training will be measured prior to implementation.
B. Self-efficacy	Individual belief in their own capabilities to execute courses of action to achieve implementation goals.	Self-Efficacy Survey (Winter 2022)	--	ECE students’ perceived self-efficacy to successfully complete the e-Learning course will be measured prior to implementation.
C. Individual Stage of Change	Characterization of the phase an individual is in, as he or she progresses toward skilled, enthusiastic, and sustained use of the intervention.	Demographics Survey, Program Evaluation Survey (Winter 2022)	--	ECE students’ motivation to learn about physical activity and sedentary behaviour will be measured pre- and post-intervention, as well as their likelihood of using the knowledge they gained in their future profession.
D. Individual Identification with Organization	How individuals perceive the organization, and their relationship and degree of commitment with that organization.	Demographics Survey (Winter 2022)	--	ECE students’ level of commitment to their studies will be measured as part of participant demographics.

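### Section 2.10.7 treats completing the CFIR checklist as a sign of scalability, but as worded the inference does not depend on how many constructs are fulfilled

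*Protocol article*

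**What the plan says.** Section 1.2 lists, as part of the second secondary objective, "potential scalability (via the Consolidated Framework for Implementation Research (CFIR) checklist) of the e-Learning course". No other instrument is named for scalability.

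Section 2.10.7 has research staff complete the checklist. It explains that "The research team will document how each construct of the CFIR" is satisfied, "using data from the needs assessment, the Delphi content development study, website metrics, process evaluation survey, and interviews". It then draws the inference: "Completion of this checklist will be indicative of the scalability of the TEACH study to a wider population".

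Section 2.3 makes the same link in other words: adherence to the CFIR constructs during the project is itself taken as a marker of scalability. Section 2.12.2 provides only for descriptive statistics on the checklist data.

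Appendix C shows the form. Each row has a construct, a short description, a source, a column asking whether the construct was fulfilled, and a column saying how it was or will be fulfilled. Table 1 schedules the checklist at baseline, post-course and 3-month follow-up in both groups.

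**The concern.** An inference about scalability should be able to come out unfavourable. Here the thing that counts is that the form is completed, and the people who complete it belong to the team that built the course. The text asks them to record how each construct is met rather than whether it is. No passage describes a checklist result that would count against scaling up.

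The conclusion has an audience. Section 4 sends the results to colleges, universities and policymakers, and the External Policy & Incentives row of Appendix C aims at adoption of the training across the profession. If scalability is reported because the checklist was completed, those readers may take it as a finding about uptake, fidelity and acceptability when it need not be one.

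**Working it through.** This is a matter of reading and counting; no sample size or error rate enters.

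**Step 1: reproduce the plan's figure.** Section 2.10.7 gives 39 constructs. The Appendix C rows by domain are 8 (intervention characteristics) + 4 (outer setting) + 14 (inner setting) + 5 (individuals) + 8 (process) = 39. The figure is reproduced.

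**Step 2: count the rows that can be rated.** Three rows are parent headings with empty cells: Implementation Climate, Readiness for Implementation, and Engaging. 39 − 3 = 36.

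**Step 3: count their present status.**

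| Domain | Yes | Open | No |
|---|---|---|---|
| I | 4 | 4 | 0 |
| II | 1 | 3 | 0 |
| III | 5 | 7 | 0 |
| IV | 0 | 5 | 0 |
| V | 0 | 7 | 0 |
| Total | 10 | 26 | 0 |

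10 + 26 = 36, so 10/36 = 28% are already marked as fulfilled.

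**Step 4: see what the 10 rest on.** Five cite the needs assessment or the Delphi study: Intervention Source, Evidence Strength & Quality, Relative Advantage, Tension for Change, and Compatibility. Section 2.10.7 names both studies as sources, so marking these rows early is legitimate. The other five (Cost, Cosmopolitanism, Structural Characteristics, Networks & Communications, Culture) cite funding, a ministry, recruitment, faculty and staff, or reputation. Two of these are plain assertion. Culture is supported by "Colleges and universities are esteemed to provide high-quality educational experiences", and Networks & Communications by a general statement about good working relations among staff.

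**Step 5: see what would fulfil the open rows.** Three examples show the pattern:

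- Complexity: students and instructors are to be asked how easy the course was to complete or implement.
- Executing: dose received is to be calculated from module completion, with no minimum.
- Self-efficacy: confidence to complete the course is to be measured beforehand.

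Each entry is met by carrying out the activity. As an illustration with assumed values, module completion of 20% and of 95% would satisfy the Executing entry equally.

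**Step 6: apply the rule under both readings.**

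- *Completion means the form is filled in.* A finished form with any number of fulfilled constructs from 0 to 36 is equally indicative of scalability. The rule does not discriminate.
- *Completion means all constructs are fulfilled.* The rule can fail, for instance if a planned survey is not run. Rows like those in Step 5 would still test whether something was done rather than what it showed. The text does not state this reading.

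**The case against.** The strongest reply is that the form itself asks whether each construct was fulfilled, leaves 26 rows open, and draws partly on participant data, so an unfavourable entry can be recorded. Table 1 schedules the checklist at three time points, so early entries need not be final. This stands, and it rules out a stronger reading. A reader might infer that a favourable scalability conclusion is certain whatever the trial finds. That depends on taking completion to mean only that the boxes are filled, and the documents do not settle this.

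Poor uptake would also not be hidden. Completion rates and usage are collected (section 2.10.2), student acceptability and compatibility are surveyed (2.10.4), instructors rate feasibility (2.10.5), and both groups are interviewed (2.10.6). Section 2.3 and the Conclusions make scaling and translation conditional on effectiveness. The objective is exploratory and the wording is cautious. All of this limits the harm, but none of it changes the sentence that links completion to scalability.

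A reader might also infer that the checklist relies on data that will not be collected, since one row says students' "level of commitment to their studies will be measured as part of participant demographics" while section 2.10.1 lists no such item. That list is introduced as illustrative, and a condensed article may omit items, so the documents do not support the charge.

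Finally, detailed rating rules may sit in a fuller protocol. The point here is different: the article states an inference, and the inference as stated is weak.

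**Conclusion.** The concern holds in a limited form. Sections 2.10.7 and 2.3 tie scalability to completing or following the checklist, the stated rule does not use the fulfilment column, and many entries are met by activity rather than result. As worded, the inference discriminates poorly between a course that is ready to scale and one that is not.

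The size is small. It affects the scalability half of one exploratory secondary objective. Fidelity, feasibility and acceptability have their own instruments, and the primary outcomes and sample size are unaffected. The 10 rows already marked as fulfilled are weak evidence of a problem taken as a group, because half cite proper prior studies; only a few, such as Culture and Networks & Communications, rest on assertion. The conclusion assumes that the article's wording reflects how the checklist will actually be used.

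**What to change.** Replace the closing sentence of section 2.10.7 with wording such as:

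> After the trial each construct will be rated fulfilled, partly fulfilled or not fulfilled from the results of its named data source (module completion, process surveys, interviews). Potential scalability will be discussed from that pattern, with unfulfilled constructs reported as barriers. Completion of the checklist is not itself evidence of scalability.

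Bring the last sentence of section 2.3 into line with it.

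The change is to wording only and relies on data already planned. The price is that the scalability statement may be less favourable than under the present text.

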### 2.11. Pilot Testing

To ensure the e-Learning course is functional, easy to use, and has a reasonable time commitment, we will pilot test the course, first, with ~150 in-service ECEs (from across the country, recruited via social media), and second, with pre-service ECEs attending college/university in two provinces and one territory (~50 students). While the course is designed for the pre-service ECE population, pilot testing in a sample of in-service ECEs will be undertaken to ensure the course provides them with relevant and useful education to support ECEs’ programming of active opportunities in a variety of childcare settings (and if effective, to support future implementation with this population). Participants will complete the e-Learning course and will be asked to complete an online survey post-intervention to gather specific feedback on the course’s functionality and pre- and in-service ECEs’ satisfaction with the course content and design. Semi-structured interviews with pre-service (~8) and in-service ECEs (~8) will be conducted post-intervention to gather more in-depth information on their experiences with the course. Additionally, to explore preliminary efficacy of the intervention, a secondary objective of the pilot study will be to measure changes in participants’ physical activity and sedentary behaviour-related: 1. self-efficacy; 2. knowledge; and 3. behavioural intention and perceived behavioural control (via online survey at pre- and post-intervention). After identifying strengths and weaknesses of the e-Learning course, appropriate changes will be made prior to full-scale implementation. Pilot testing is currently underway, with full scale implementation targeted to begin in September 2022.

### 2.12. Data Analyses

Baseline characteristics of the pre-service ECEs and their physical activity programming offerings (based on the curriculum review) will be summarized descriptively. Group differences at baseline will be assessed by independent sample *t*-tests or chi-square tests, as appropriate. If applicable, group differences on baseline measures will be statistically controlled in subsequent analyses (e.g., gender, age, and amount (number of course hours and content areas covered) of physical activity and screen-viewing training provided by the college/university). 

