## 2. Methods

### 2.1. Study Design

A mixed-methods quasi-experiential design will be employed to test the effectiveness of the TEACH e-Learning course at improving pre-service ECEs’ physical activity and sedentary behaviour-related self-efficacy and knowledge. Purposefully selected English-speaking colleges/universities offering an early childhood education program in Canada (i.e., clusters) will be randomly assigned to the experimental (*n* = 9) or comparison (*n* = 9) condition. A 4-module e-Learning course (hosted on a secure learning management system platform) will be implemented by schools assigned to the experimental condition, while comparison schools will continue with their typical curriculum. Data will be collected at baseline, post-course completion, and 3-month follow-up. The study protocol and tools for the study have been approved by the Non-Medical Research Ethics Board (initial REB# 116816; January 2021) at Western University and ethics approval for the full-scale implementation will be sought prior to recruitment and data collection. Additional approval from participating college/university ethics boards will be completed, if requested

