### 2.5. Recruitment and Allocation

#### 2.5.1. Universities and Colleges with ECE Programs

To help ameliorate potential recruitment challenges and secure a diverse sample with representation from a number of Canadian provinces, we will draw on our established rapport with early childhood education post-secondary programs and will purposefully select colleges/universities (see sample size explanation below) and recruit their ECE programs to participate by emailing ECE program coordinators. Once 16 colleges agree to participate, allocation to the experimental and comparison conditions will occur. To safeguard the internal validity of the intervention, it is important to avoid randomly allocating individuals within each college to receive the training (or not), given the e-Learning course may be completed during pre-service ECEs’ class time and contamination may occur. As such, participating colleges/universities will act as the unit of randomization (i.e., clusters). Once consent has been obtained from the college/university representative (e.g., program coordinator/chair), the clusters will be stratified by province, college/university size, and college/university ECE program delivery mode (i.e., in-person, online, or blended learning). Blocked randomization will be performed to allocate clusters (1:1) using a computer-generated randomization tool (www.randomizer.org (accessed on 12 March 2022); the software will generate a number of 1 or 0) to either receive the training (experimental; “1”) or not (comparison; “0”).

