### 2.7. Sample Size

We used the ‘pwr’ package in R [38,39] to estimate the sample size for the analyses (Primary Objectives #1 and #2). These calculations suggest that we need 224 pre-service ECEs (112 per group) to detect a small-to-medium effect size (f^2^ = 0.053 or R^2^ = 0.05), with 2 groups (intervention and control) and 3 time-points (baseline, post-intervention, follow-up), 80% of the time, with an alpha of 0.025. As we will target college/university programs as units (clusters), the sample size will be adjusted to account for the clustering effect, where: D = design effect; *k* = anticipated cluster size (class size in this case); and *ρ* = the intra-cluster correlation coefficient, a measure of the degree of homogeneity among cluster subjects for a particular outcome investigated.
D = 1 + (*k* − 1) *ρ* = 1 + (164 − 1) (0.05) = 9.15

We estimate an average class size of 164 pre-service ECEs (based on our nationwide study of pre-service ECEs from 61 colleges; [19]). Based on a preliminary scan of early childhood education programs in Canada, programs across the country have comparatively similar curriculum; therefore, the intra-cluster correlation coefficient will be lower. For the purpose of estimating this sample size, we assumed a value of 0.05. Thus, the design effect is 9.15, and the sample size needs to be inflated. Finally, the sample will be further adjusted to account for loss to follow-up at 3 months (~30% attrition rate); therefore, the final targeted sample size will be 112 × 9.15/0.70 = 1464 ECE students per group.

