#### 2.12.1. Primary Outcomes

Pre-service ECEs’ physical activity and sedentary behaviour-related self-efficacy and knowledge will be evaluated using two (self-efficacy, knowledge) linear mixed effects models wherein group and time are our primary fixed effects. Demographic variables will be used as predictors of pre-service ECEs’ self-efficacy, knowledge, and behavioural intention and perceived behavioural control in our analyses. Specifically, we will explore the extent to which province/territory predicts the dependent variables, and whether there is a significant effect of previous training, early childhood education program type, and mode of delivery. Based on previous research, the pre-service ECE population is largely female [19], so gender-based differences will not be explored. Finally, if baseline differences are observed, we will include student age, physical activity, and sedentary time as covariates in all models. 

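### Conditional covariates are chosen by baseline t-tests and chi-square tests that ignore college clustering; replace the rule with one fixed covariate set

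*Protocol article*

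**What the plan says.** All references are to the protocol article.

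- Section 2.12 names the method: "Group differences at baseline will be assessed by independent sample *t*-tests or chi-square tests". It then makes the result act: "If applicable, group differences on baseline measures will be statistically controlled in subsequent analyses". Its examples are gender, age and the amount of relevant training that the college provides.
- Section 2.12.1 carries this into both primary models: "if baseline differences are observed, we will include student age, physical activity, and sedentary time as covariates in all models". Section 2.12.2 repeats the same three covariates, again conditionally, for behavioural intention and perceived control.
- Section 2.1 says that colleges and universities "will be randomly assigned to the experimental (*n* = 9) or comparison (*n* = 9) condition", and section 2.5.1 confirms that the institution is the unit of randomisation.
- Section 2.7 allows for clustering in the sample size: "We estimate an average class size of 164 pre-service ECEs", an assumed ICC of 0.05 and a design effect of 9.15.
- Section 2.10.1 lists "self-reported physical activity and recreational screen-viewing levels" among the variables collected. It does not list sedentary time.

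No cluster adjustment and no significance level is given for the baseline tests.

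**The concern.** Two faults are combined.

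First, the tests do not fit the design. Students in one college share a curriculum, a region and an intake, so their values are correlated. A t-test or chi-square test that treats them as independent understates the standard error of the difference between arms and declares differences too often. The plan inflates its sample size roughly ninefold for this reason and then sets clustering aside for the baseline comparison.

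Second, the rule would be poor even with a valid test. A covariate earns its place by predicting the outcome, not by the p-value of its imbalance. Under this rule, of the conditional covariates, a strong predictor that happens to balance is left out and a weak one can enter on a false flag. The selection is driven by the data, and the standard error reported from the final model does not reflect it.

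The candidate list is also unsettled. Section 2.12 gives gender, age and training amount as examples, while section 2.12.1 gives age, physical activity and sedentary time and sets aside gender-based differences. At stake is whether the adjusted primary estimates can be called prespecified.

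**Working it through.** **Inputs from the plan.** Cluster size k = 164, ICC ρ = 0.05, 112 students per group before inflation, 30% attrition (section 2.7); 9 colleges per arm (section 2.1).

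**Inputs assumed.** A 5% two-sided level for the baseline tests, with 2.5% also shown. The ICC of baseline variables is not given, so a range is used.

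**The plan's own figures.**
- D = 1 + (164 − 1) × 0.05 = 9.15, as stated.
- 112 × 9.15 / 0.70 = 1464 per group, as stated.
- 1464 / 9 = 162.7 students per college, which agrees with k = 164.

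**False-flag rate.** With no true difference between arms, the test statistic that ignores clustering has standard deviation √D instead of 1. The chance of a flag is 2[1 − Φ(z/√D)], with z = 1.96 at the 5% level.

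At ρ = 0.05: 1.96 / √9.15 = 0.648, and 2[1 − Φ(0.648)] = 0.517. At the 2.5% level it is 0.459.

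| Assumed ICC (k = 164) | D | Flag rate at nominal 5% |
|---|---|---|
| 0 | 1.00 | 5% |
| 0.01 | 2.63 | 23% |
| 0.02 | 4.26 | 34% |
| 0.05 | 9.15 | 52% |
| 0.10 | 17.30 | 64% |

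**Cluster size.** At ICC 0.05 and k = 100, D = 5.95 and the rate is 42%. Section 2.5.1 allocates once 16 colleges agree. With 8 per arm, 1464 / 8 = 183 students per college, and the rate is 54%.

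**Simulation check.** In 20,000 simulated trials with 9 colleges of 164 per arm and ICC 0.05, the student-level t-test flagged 51.9%. The chi-square test flagged 52.1% at a prevalence of 30% and 51.3% at 10%. A t-test on the 9 versus 9 college means flagged 4.9%, so the excess comes from ignoring clustering.

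**Three named covariates.** If they were independent, the chance that at least one is flagged is 1 − (1 − 0.517)³ = 0.89 at ICC 0.05, and 1 − (1 − 0.227)³ = 0.54 at ICC 0.01. Section 2.12.1 does not say whether one flag brings in all three.

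**The case against.** **The 52% borrows an outcome ICC.** Section 2.7 defines the ICC for an outcome and gives none for age, physical activity or screen-viewing. Participation is voluntary, and the earlier national survey in the Background had 1292 respondents from 61 colleges, about 21 each. At k = 21 and ICC 0.05, D = 1 + 20 × 0.05 = 2.0 and the rate is about 17%; at ICC 0.01, D = 1.2 and it is about 7%. Stratified allocation may lower it further. This stands: the size is conditional. However, k = 164 is the plan's own figure and is what its target of 1464 per group requires.

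**Over-flagging pushes towards adjustment.** If one flag brings in all three covariates, the result is often close to always adjusting. This is fair, and no effect on the bias, type I error or power of the primary test has been computed. It does not make the covariate set prespecified.

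**Stronger readings that the documents do not support.**
- *The primary model is picked by chance.* Group and time are in the models whatever the tests show, and section 2.12.1 examines province, previous training, program type and delivery mode without that condition. Only the conditional covariates vary.
- *Any baseline difference is chance.* This holds for the allocation of colleges. Sections 2.5.1 and 2.5.2 leave open that students enrol after allocation, through staff not stated to be blind to it. Differences between students could then be systematic. That does not rescue a test with a high false-flag rate, which cannot tell recruitment bias from chance.
- *College-level training is tested as if it were about 2,900 student values.* Such a test would flag about 88% (D = 164). But Table 1 lists the curriculum review at university/college level, and the article does not say that the test would be run per student. On 18 college values there is no such inflation.
- *Sedentary time is not collected.* The full demographic survey is not reproduced. The text supports only a mismatch of labels with recreational screen-viewing.

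**Conclusion.** The point holds as a stated method that should be changed. Sections 2.12 to 2.12.2 tie covariate selection to baseline differences, and the only method named for finding them ignores the clustering that section 2.7 accepts. On the plan's own ICC and cluster size, about half of baseline variables with no true difference would be flagged at a nominal 5% level. This rests on carrying the outcome ICC over to baseline variables, on a 5% level, and on about 164 responding students per college. At that cluster size even an ICC of 0.01 gives more than four times the nominal rate, though clusters of about 21 would bring it near nominal at that ICC. The second fault, choosing covariates by a test of balance, depends on none of these assumptions. The consequence is a conditional covariate set that is not fixed in advance in either the primary or the secondary models; the size of any effect on the primary test itself is not established.

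**What to change.** 1. In section 2.12, report baseline characteristics by arm descriptively and remove the significance tests.
2. In sections 2.12, 2.12.1 and 2.12.2, delete the rule that makes adjustment depend on observed baseline differences.
3. Before outcome data are seen, name one covariate set for all models, used whatever the balance: age, baseline physical activity, baseline recreational screen-viewing, and a small number of the stratification factors (province, size, delivery mode) that 18 colleges can support. Reconcile screen-viewing in section 2.10.1 with sedentary time in sections 2.12.1 and 2.12.2, so that the covariate is a variable actually collected.
4. State how the baseline outcome is handled, because baseline is already one of the three time points. Either keep it as an outcome time point with baseline means constrained equal across arms, or use it as a covariate with only the two later times as outcomes. Do not do both.

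The cost is a short rewrite of the analysis section and a few degrees of freedom. The between-college ones are scarce with 18 clusters, which is why full adjustment for every stratum is not proposed. No new student data are needed if screen-viewing is the covariate.
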